### Outcomes

The primary objectives of this study are to identify the most effective and feasible approach for screening contacts of patients with leprosy in combination with administering chemoprophylaxis to prevent leprosy (table 3). Because of the long incubation period of leprosy, it will not be possible to observe reduced transmission at the population level, in terms of a reduced new case detection rate, during this project period. The active case finding component and raised awareness, however, are expected to lead to more detected cases, improved early case detection and disability rates at time of diagnosis. We hypothesise that enhanced case finding and integrated skin screening will lead to an overall reduction of detection delay primarily in the community-based intervention over the study duration, driven by the diagnosis of patients with early signs of leprosy (and shorter delays) that would otherwise go undetected.

**Table 3 T3:** PEP4LEP project outcomes and methods of analysis

Objective	Outcome	Hypothesis	Outcome measure	Method of analysis
1.1 To compare the effectiveness of a skin camp prophylaxis intervention with a health centre-based prophylaxis intervention in terms of the rate of patients with leprosy detected and delay in case detection	Primary: Case detection delay	Reduction in case detection delay is expected to be greater in the community-based intervention compared with the health centre-based household contact approach	Number of months since first signs or symptoms of leprosy until diagnosis (including assessing both ‘patient delay’ and ‘health-system delay’); G2D percentage among newly diagnosed patients with leprosy	Descriptive statistics; multivariate models; non-parametric tests
	Primary: Number of contacts diagnosed with leprosy	The community-based intervention will identify more cases of leprosy from contact screening compared with the health centre household contact-based approach	Number of contacts diagnosed with leprosy; child proportion; female proportion; MB/PB classification of newly diagnosed patients with leprosy	Descriptive statistics; Pearson’s χ^2^ test; Fisher’s exact test; multivariate logistic regression analysis

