### Sample size

The sample size calculation was based on case detection delay as the main outcome measure for comparing the effectiveness of each intervention. This measure was used for the calculation because the epidemiological impact (ie, reduction in overall new case detection rate in PEP4LEP districts) will not become apparent within the study duration due to the long incubation time of leprosy. The mean or median delay will be compared between both interventions and with the baseline. A baseline case detection delay will be estimated in each country by interviewing recently diagnosed patients with leprosy with the same structured questionnaire prior to the start of the study. For the sample size calculation, a literature-based estimated average case detection delay of 24 months for patients with leprosy with a SD of 8 months was used, with the conservative assumption that a minimal delay difference of 3 months would be detected between both interventions.^73 74^ In order to achieve this, we aim to include at least 675 index patients in the study: 270 in the community-based intervention areas (30 per country per year) and 405 new patients in the health centre-based intervention areas (45 per country per year). Approximately 100 contacts will be screened per index patient in the community-based intervention areas, and approximately 6 contacts will be screened per index patient in the health centre-based intervention areas; thus, a total of approximately 30 000 contacts will be screened (figure 3). We expect no major differences in case detection delay between clusters and within clusters, hence no significant design effect is foreseen. For the feasibility study component and additional research objectives, interviews and FGDs are planned. For the interviews, a minimum of 10 index patients, 10 household contacts, 10–20 community contacts, 10 health workers/community volunteers, 4 health decision-makers and 10 community leaders will be included. For the FGDs, 6–10 participants will be included: two groups of index patients, two groups of household contacts, two groups of community contacts, two groups with health workers and one to two groups with decision-makers. Contacts refusing to receive skin screening and/or take SDR-PEP, but who are willing to participate in the qualitative study component and community members outside of the 20 closest houses to the index patient in intervention one will also be included. The qualitative research sampling will be purposive, according to the defined target groups, and balanced according to, for example, gender, age, education level, religion and/or socio-cultural background. All fully trained health staff involved in the PEP4LEP project will be asked to consent to enrol in the capacity assessment.

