
### Randomisation

PEP4LEP used randomisation without blinding at the (clustered) health centre level (health centres/posts), ensuring that clusters were similar in size. There are 17 health facilities included in Ethiopia, 22 in Mozambique and 23 in Tanzania. Blinding is not possible because of the varying operational components of the interventions. Cluster randomisation is commonly used when trying to capture the impact of an intervention at community level on both infectiousness and susceptibility.^75^ This method is stated to be feasible logistically, and contamination (eg, information-sharing between participants from both interventions) is unlikely.^75^ Randomisation was performed using the statistical software package R.^76^ Per country, health centres were randomly divided into the community-based intervention or health centre-based intervention.

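### Health centres are randomised, but the design effect is set aside on an unsound argument and no test named for the between-arm comparisons allows for clustering

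*Protocol article*

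**What the plan says.** The Randomisation section makes the health facility the allocated unit: "PEP4LEP used randomisation without blinding at the (clustered) health centre level (health centres/posts), ensuring that clusters were similar in size". It gives the numbers, "There are 17 health facilities included in Ethiopia, 22 in Mozambique and 23 in Tanzania", and the stratum: "Per country, health centres were randomly divided into the community-based intervention or health centre-based intervention".

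The Sample size section uses an "estimated average case detection delay of 24 months for patients with leprosy with a SD of 8 months was used" and supposes that "a minimal delay difference of 3 months would be detected between both interventions". It plans 270 index patients in the community arm and 405 in the health centre arm, with about 100 and 6 contacts screened per index patient. On clustering it says only this: "We expect no major differences in case detection delay between clusters and within clusters, hence no significant design effect is foreseen".

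Table 3 (Outcomes) gives the analysis of delay as "Descriptive statistics; multivariate models; non-parametric tests". For contacts diagnosed with leprosy, and again for contacts diagnosed with other skin diseases, it lists descriptive statistics and Pearson's chi-square, followed by "Fisher’s exact test; multivariate logistic regression analysis". Contacts screened and given SDR-PEP are to be described only. The Data analysis section adds two-tailed tests at 0.05 and 95% confidence intervals for regression. No mixed model, GEE, robust variance or cluster-level summary appears anywhere.

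**The concern.** When facilities are randomised, patients and contacts of one facility tend to resemble each other, and the uncertainty of the arm comparison is governed largely by variation between facilities. An ordinary chi-square, Fisher or logistic analysis counts every contact as an independent observation and so understates the standard error.

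The reason given for setting this aside does not carry the conclusion. Small differences between clusters would be a proper premise. Small differences within clusters would not, because for a given between-cluster variance, less variation within clusters raises the ICC. Nor can both be small when the SD is 8 months, since that variance has to lie somewhere. The article's own definition of delay also includes a health-system part, from first consultation to diagnosis (Case detection delay section). That part can plausibly differ by facility, which is the randomised unit.

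At stake is whether a nominally significant difference in a primary outcome means what its p value says.

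**Working it through.** **Inputs from the article.** Clusters: 17 + 22 + 23 = 62. Index patients: 270 + 405 = 675. Contacts: 270 × 100 = 27,000 and 405 × 6 = 2,430, together 29,430 (stated as about 30,000). SD 8 months, difference 3 months, two-sided 5%.

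**Assumptions, not in the article.** Each facility is one cluster, with 31 per arm and equal sizes. The ICC is shown as a range. A normal approximation is used.

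**The plan's own figure.** No power is stated, so 675 cannot be reproduced from the stated inputs alone. With n per arm = 2(1.96 + 0.84)² × 8²/3², 80% power needs 112 per arm, 224 in all. With 270 and 405, SE = 8√(1/270 + 1/405) = 0.629, and power = Φ(3/0.629 − 1.96) = 99.75%. Sizing each country separately at 80% and 1:1 would give 3 × 224 = 672, close to 675, but the article states neither the 80% nor per-country sizing. No variant contains a design effect.

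**Delay.** Index patients per cluster: 270/31 = 8.7 and 405/31 = 13.1 (average 675/62 = 10.9).
- Design effect per arm: DE = 1 + (m − 1) × ICC.
- Variance ratio: R = (DE₁/270 + DE₂/405) / (1/270 + 1/405).
- True error of an unadjusted 5% test: 2[1 − Φ(1.96/√R)]. Coverage of a nominal 95% interval is 1 minus this.
- Implied between-centre SD: 8√ICC.

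Example at ICC 0.05: DE₁ = 1.39, DE₂ = 1.60, R = 1.473, √R = 1.214, and 1.96/1.214 = 1.615, so the error is 10.6%.

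| ICC | Between-centre SD (months) | Average DE | √R (CI width factor) | True error | Coverage | Pooled power, valid test |
|---|---|---|---|---|---|---|
| 0.01 | 0.8 | 1.10 | 1.05 | 6.1% | 93.9% | 99.5% |
| 0.02 | 1.1 | 1.20 | 1.09 | 7.2% | 92.8% | 99.2% |
| 0.05 | 1.8 | 1.49 | 1.21 | 10.6% | 89.4% | 97.6% |
| 0.10 | 2.5 | 1.99 | 1.40 | 16.0% | 84.0% | 92.8% |
| 0.20 | 3.6 | 2.98 | 1.70 | 24.9% | 75.1% | 80.2% |

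Centre means that vary with an SD of only 0.8 to 2.5 months around an average of 24 are enough to give an ICC of 0.01 to 0.10.

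**Contacts diagnosed with leprosy.** Contacts per cluster: 27,000/31 = 871 and 2,430/31 = 78. The formulas are the same, with 27,000 and 2,430 as denominators and equal proportions in the two arms under the null.

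| ICC | DE community | DE health centre | √R | True error |
|---|---|---|---|---|
| 0.001 | 1.87 | 1.08 | 1.07 | 6.7% |
| 0.002 | 2.74 | 1.15 | 1.13 | 8.4% |
| 0.005 | 5.35 | 1.39 | 1.31 | 13.4% |
| 0.01 | 9.70 | 1.77 | 1.56 | 20.8% |

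**The case against.** Several points on the other side stand and limit the finding.

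- **Scope.** A reader might infer that every between-arm comparison is affected. That is not so: the number of contacts screened and given SDR-PEP, also a primary outcome, has no planned test.
- **Delay methods.** A reader might infer that delay will certainly be analysed as if patients were independent. Table 3 does not say so. A multivariate model can contain a health-centre term, a rank test can be run on centre summaries, and an analysis plan not shown here may specify either. Only the ordinary chi-square and Fisher tests firmly exclude clustering.
- **Wording.** The article does not deny clustering outright. It foresees no significant design effect, for delay only, and is silent on contact outcomes.
- **Other statements in the article.** Focal distribution of cases (Study setting) and clustering within households (health centre-based intervention section) concern where disease occurs. They bear on contact outcomes and do not contradict an expectation about delay.
- **Size.** The inflation rests wholly on assumed ICCs. At the low ends the error is only 6–7%.
- **Contact null.** The article says household contacts run a higher risk than the general community, so equal proportions in the two arms is not a realistic null. The false-positive figure therefore matters less for this outcome, but standard errors and intervals would still be understated.
- **Power.** A reader might infer that the trial is too small. With all countries pooled and SD 8, it is not. If 675 was meant to give about 80% power in each country, 90 against 135 gives 78.7% without clustering and 62.2% at ICC 0.05, but the article does not state that aim.

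What remains cannot be put down to condensed reporting. The article gives a reason for setting the design effect aside, and that reason is unsound. It also names individual-level tests for a primary contact outcome.

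**Conclusion.** The concern holds for the comparisons that carry a test or a confidence interval: delay, contacts diagnosed with leprosy, and contacts diagnosed with other skin diseases. For the contact outcomes it follows from the tests named. For delay it follows if the dismissal of the design effect is carried into the analysis, which nothing in the article prevents.

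The direction is certain for any positive ICC; the size is not. For delay, ICC 0.01–0.10 gives a true error of about 6–16% and coverage of about 94–84%. For contacts diagnosed with leprosy, ICC 0.001–0.01 gives an error of about 7–21%. Unequal cluster sizes would raise the design effect. So would fewer clusters at the same ICC, for instance if facilities were grouped before randomisation. The problem is the validity of inference, not the pooled number of patients.

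**What to change.** 1. **Sample size section.** Replace the sentence on the design effect with an assumed ICC range for delay and the design effect it implies at about 11 index patients per centre.
2. **Table 3, contacts diagnosed (leprosy and other skin diseases).** Replace chi-square, Fisher and ordinary logistic regression with mixed or GEE models that take health centre as the cluster and also allow for clustering by index patient, or with cluster-summary tests.
3. **Table 3, delay.** Specify a health-centre random effect, or an analysis of centre summaries, on a scale that suits the planned comparison of means or medians.
4. **Throughout.** Account for country as the randomisation stratum, use a small-sample correction for the number of clusters, and report the observed ICC for each outcome.

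The cost is a change of wording and wider intervals: for delay, about 5% wider at ICC 0.01 and about 40% wider at ICC 0.10. No additional patients are needed under the article's SD of 8, since pooled power for 3 months is 92.8% at ICC 0.10 and 80.2% at ICC 0.20.

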
### Randomisation

PEP4LEP used randomisation without blinding at the (clustered) health centre level (health centres/posts), ensuring that clusters were similar in size. There are 17 health facilities included in Ethiopia, 22 in Mozambique and 23 in Tanzania. Blinding is not possible because of the varying operational components of the interventions. Cluster randomisation is commonly used when trying to capture the impact of an intervention at community level on both infectiousness and susceptibility.^75^ This method is stated to be feasible logistically, and contamination (eg, information-sharing between participants from both interventions) is unlikely.^75^ Randomisation was performed using the statistical software package R.^76^ Per country, health centres were randomly divided into the community-based intervention or health centre-based intervention.

### Data collection and management

The PEP4LEP data management plan was developed by Erasmus MC in collaboration with the consortium members. Regarding quantitative data, collectors will record their findings onto paper-based forms. Information from the forms will be entered into the Research Electronic Data Capture (REDCap) system from Vanderbilt University.^77^ The REDCap software will be linked to a centralised database server hosted by Erasmus MC.

To determine the cost-effectiveness, data for establishing costs (such as infrastructure, human resources, transportation) and output (such as number of contacts seen, rifampicin capsules provided, patients diagnosed with other NTD-related skin diseases and treatments provided) will be derived from the ongoing surveillance data. Other costs (such as general programme costs, treatment costs and other direct or indirect costs) will be collected from ancillary studies.

Besides quantitative data, qualitative data will also be collected for the acceptability and health workers’ capacity assessment. Data from (semi-)structured interviews, FGDs and possible ethnographic observations will be audio-recorded and/or paper-based. Data will be transcribed (verbatim), translated to English and entered into computer-assisted qualitative data analysis software.^78^ The transcriptions will be securely stored at Erasmus MC after analysis. A system of identification (ID) codes has been developed to record and maintain data systematically, as well as to maintain ‘pseudo-anonymity.’

### Data analysis

Data from the PEP4LEP study will be analysed primarily through quantitative methods using descriptive analysis for all variables (table 3). Mean or median case detection delays will be compared between both interventions and the established baseline. This includes newly diagnosed cases identified through each contact screening intervention as well as those detected through ongoing passive case finding, currently the primary method of detection in routine leprosy programmes in the three countries. The p values for each statistical test will be two-tailed with p≤0.05 considered significant and 95% CIs presented for regression analyses. Quantitative analysis will be conducted using statistical software such as SPSS.^79^

The acceptability and capacity assessments will include qualitative research data (table 3), which will be coded and analysed using computer-assisted qualitative data analysis software, including Atlas.ti.^78 80^ Data coding is necessary to categorise and define what the data signify by identifying concepts, patterns, relations and themes.^81^ Data reanalysis will occur until no new topics are emerging and data saturation is reached, which means that no significant new themes are emerging.^82^

### Availability of data and materials

Data will be stored for 25 years according to EU regulation 536/2014 considering clinical medication-related research projects.^66^ Data will be made available in a repository for potential authorised reuse for future data analysis or study replication. Sharing data and study materials as well as open access publishing are important values of the EU research and innovation programme Horizon 2020, the European and Developing Countries Clinical Trials Partnership and the PEP4LEP consortium.^66 83^ Study materials will be made available via https://www.infolep.org, the international knowledge centre for information resources on leprosy, and via https://www.infontd.org, the one-stop portal of information on cross-cutting issues in NTDs.^84 85^

### Patient and public involvement

Community leaders, people affected by leprosy and representatives of disabled people organisations are involved in monitoring the study as well as in mobilising community participation. Results will be reported back to the communities via community workshops. Capacity building is an important part of this project. Besides training health staff and community volunteers, four PhD-candidates will obtain a PhD from this project, of which three candidates originate from the endemic countries included in this project to increase local research capacity.^60^

### Ethics

Ethical approval was obtained in each country according to national guidelines (table 4). Erasmus MC, as European consortium member, received a waiver of full medical ethics review and approval from its ethical board according to the Dutch Medical Research Involving Human Subjects Act (Wet Medisch-Wetenschappelijk Onderzoek met mensen).^86^

**Table 4 T4:** PEP4LEP ethical approvals

Country	Ethical board	Outcome	Primary approval/waiver date
Ethiopia	National Research Ethics Review Committee from the Ministry of Science and Higher Education (MoSHE)	Approved	17 February 2020
Mozambique	Comité Nacional de Bioética para a Saúde (CNBS) from the Ministério da Saúde	Approved	16 August 2019
Tanzania	Ethical Clearance Committee linked to the National Institute for Medical Research (NIMR) and Ministry of Health, Community Development, Gender, Elderly & Children (MoHCDEC)	Approved	17 June 2019
The Netherlands	Medical Ethics Committee Erasmus University Medical Center Rotterdam (Erasmus MC)	Waiver	11 April 2019

Written (or thumbprint) informed consent will be obtained from all study participants. If a participant is below 18 years old, a parent or legal guardian will be asked for consent. Study information given to the study participants prior to asking for consent contains details about: leprosy; the study purpose; the right to withdraw; anonymity of the disease status in the community intervention; the fact that SDR-PEP leads to a leprosy risk reduction and not absolute prevention (ie, awareness of leprosy signs/symptoms remains important after taking SDR-PEP); possible side effects of SDR-PEP (ie, urine discolouration) and adverse events (AEs); the incidental findings procedure; data privacy/safety and national contact information. AEs are expected to be rare after SDR-PEP. In the LPEP study, in which SDR-PEP was administered to 151 928 screened contacts, a single AE was reported (an allergic reaction to rifampicin in Brazil) and no SAEs were seen.^13^ Urine discolouration, a common rifampicin side effect, was not considered as an AE requiring follow-up in LPEP. Nevertheless, in (chemo)prophylaxis programmes AEs are of utmost importance because large numbers of healthy individuals are involved. In PEP4LEP, SAEs will be reported following national pharmacovigilance guidelines and by using the PEP4LEP AE form for registration and to inform the principal investigator.^13 59^ The PEP4LEP project’s SOP on rifampicin administration therefore included the availability of an emergency allergy kit at community study sites where no health centre is located, which should be used according to national medical/pharmacological guidelines.^55–57^ All participants with suspected AEs will be referred for proper medical management and treated free of charge according to national standard treatment guidelines.^59^

Throughout both screening interventions and research projects involving human subjects, incidental findings with potential health importance may be observed.^87^ Incidental findings are discoveries made during a research or screening project which are outside the scope of the project.^88^ Examples of possible incidental findings when performing full body skin screening include: signs of cancer, venous insufficiency, bleeding diathesis, herniation, dental problems or indications of possible abuse. Incidental findings in a research setting are often not explicit enough to be used for diagnosis, treatment, or clinical care.^89^

The procedures for reporting both SAEs and incidental findings are included in the evidence-based PEP4LEP SOPs, on the participant information sheet and in the health workers’ training^59 87 88 90 91^ The importance will also be emphasised during ongoing monitoring activities, including field visits.^13^

During the developmental phase of this project, the COVID-19 pandemic emerged. Regarding COVID-19, national governmental and WHO guidelines will be followed.^33–36^ Information about COVID-19 and project implications (eg, physical distancing, working in time slots) are included in the project’s SOPs, information, education and communication (IEC) materials and health workers’ training. Hand washing facilities and personal protective equipment (PPE) such as gloves, face masks and aprons, will be made available at the study sides.

A code of conduct will be designed for the PEP4LEP consortium, based on the code of conducts from WHO and All European Academies.^92 93^ All researchers in the project are encouraged to participate in good clinical practice courses, facilitated by the research consortium.^94^ National data-safety monitoring boards, an international publication committee and an international scientific steering committee were formed to monitor the project (figure 1).

